## Abstract

**Abstract:**

**Purpose:**

To determine prognostic factors of disability in multiple sclerosis (MS), that is, (1) identify determinants of the dynamics of disability progression; (2) study the effectiveness of disease-modifying treatments (DMTs); (3) merge determinants and DMTs for creating patient-centred prognostic tools and (4) conduct an economic analysis.

**Participants:**

Individuals registered in the French Observatoire Français de la Sclérose en Plaques (OFSEP) database were included in this OFSEP-high definition cohort if they had a diagnosis of MS, were ≥15 years old and had an Expanded Disability Status Scale (EDSS) score <7. The outcomes will be assessed annually: (1) time to reach irreversible EDSS scores of 4, 6 and 7; (2) relapses and disease progression; (3) MRI-based progression, patient-reported outcomes, social consequences; and (4) combined outcomes on activity and progression. Clinical and quality-of-life data, MRI results and biological (blood, serum) samples will be collected at each follow-up.

**Findings to date:**

A cohort of 2842 individuals, 73.4% women, mean (SD) age of 42.7 (11.6) years, median disease duration of 8.8 years, has been recruited from July 2018 to September 2020. The course of MS was relapsing remitting in 67.7%, secondary progressive in 11.9%. The mean annual relapse rate was 0.98. The disease-modifying treatment received was highly effective therapy in 50.3% and moderately effective therapy in 30.7%.

**Future plans:**

The participants will be followed until December 2026. Disease course up to four landmarks will be examined as predictors of disease progression: (1) diagnosis of MS; (2) relapse activity worsening and independent progression; (3) any recent disease activity and (4) any visit with absence of disease activity in the past 5 years. The marginal effectiveness and tolerability of treatments will be assessed. Stratified algorithms will be proposed for medical decision-making. Economic evaluation of disease cost and cost-effectiveness of new DMTs will be conducted from a public payer perspective.

**Trial registration number:**

NCT03603457.

STRENGTHS AND LIMITATIONS OF THIS STUDYThis cohort will be unique and large enough for comprehensive analysis integrating multiple potential determinants of multiple sclerosis (MS) prognosis, including sociodemographic, clinical, imaging data and treatments.Multimodal disability including clinical, imaging and patient-reported outcomes will be the target for prediction from specific landmarks, corresponding to strategic times in MS evolution.The collection of health-related quality of life will constitute a major advantage to evaluate the usefulness of prognostic tools in stratified medicine.Statistical analysis including specific landmarks integrated into dynamic modelling will allow for developing accurate prognostic analysis over time.A maximum follow-up no longer than 8 years will be a limitation to the prediction.

## Introduction

 Multiple sclerosis (MS) is a chronic disease affecting the central nervous system. It is the most common cause of non-traumatic neurological disability in young adults. With a mean age of diagnosis of 32 years and a 2:1 ratio of women to men, about 2.9 million persons worldwide are affected^1^ and nearly 2 in 1000 individuals in France in 2021.^2^ MS leads to permanent disability for decades, with marginal effect on life expectancy.^3^ The burden of MS is huge for societies, estimated at about 14.6 billion euros per year in Europe in 2010. It is rapidly increasing with the approval and wide use of expensive new disease-modifying therapies (DMTs),^4^ reaching an annual cost burden of 2.7 billion euros in France in 2020.^5^ However, disease progression remains difficult to treat even with the most recently approved drugs.

One major unmet need for MS patients is a sufficient knowledge of the factors associated with disease progression. Also, reliable predictive tools that could be applied at the individual level and at different key moments in the disease course (landmarks) are lacking. Despite many cohort-based studies helping to identify prognostic factors and sometimes propose prognostic scores,^6^,^8^ developing a tool accurate enough to predict the many dimensions of outcomes in MS faces several challenges that have not been addressed together. Mostly issued from disease onset (ie, inception cohorts) and from data collected during routine visits to the neurologist, tools to predict long-term prognosis are hampered by intermediate evolution events (eg, relapses over time) that may modify the prognosis. A recent Cochrane review,^9^ searching for prognostic models to be used any time after diagnosis for predicting future disease course, identified 75 models that were insufficiently validated to be recommended for clinical routine use. Of note, the reports did not describe prognostication at key clinical landmarks when the neurologist needs to decide on a change in management during the disease course.

However, the gain of knowledge about many factors, particularly the progress in cerebral and spinal-cord MS lesion imaging, the standardisation and/or new definitions of clinical assessments,^10^ the genetic background^11 12^ and, above all, the recent availability of an increasing number of DMTs,^8^ may considerably change the prognosis of the disease and the ability to predict its evolution. The evolution also depends on demographic, socioeconomic context (education, profession), environmental^13^ and behavioural (alcohol consumption,^13^ smoking^14^ and eating^15^) factors.

The aim of the present study is to develop a tool accounting for this multiplicity of factors, the use of DMTs and the disease events that may occur over time for predicting clinical, MRI and patient-reported outcomes (PROs) important for both clinicians and patients with MS. Such a multidimensional approach should be applicable at significant moments (landmarks) and requires the collection of many variables at inclusion and during the follow-up of a large cohort.

Few registries or cohorts used PROs, in particular health-related quality of life (QoL), as outcomes or even prognostic factors of MS progression.^16^,^18^ Measuring the perception of the disease evolution from the patient point of view using PROs is of importance in the context of personalised medicine. It can be used to identify points that could be improved in the patient’s point of view not considered by standard clinical evaluation. In addition, QoL can be used as a prognostic tool in other diseases.^19 20^ In the scope of health-economic analysis, the national and international health authorities recommend conducting cost-utility analysis whenever QoL is a major consequence of health interventions.^21 22^

To our knowledge, with the exception of the MS PATHS initiative,^17^ a cohort similar to Observatoire Français de la Sclérose en Plaques (OFSEP), though not organised with as accurate and structured measurement times as in OFSEP-high definition (OFSEP-HD), no other cohort study of MS patients has yet proposed the prospective, multicentric and standardised collection of such multisource and multimodal data to (1) describe the disease progression and identify its determinants (ie, socioeconomic and clinical characteristics, QoL, behavioural and environmental factors, MRI, DMT use and biologic samples); 2) develop patient-centred prognostic tools for the main landmarks of MS progression and to help in decision-making; 3) evaluate the effectiveness of DMTs by clinical trial emulations; and 4) assess the cost of MS disease and the cost-effectiveness of DMTs. According to the existing OFSEP initiative,^23^ the main innovative feature of the OFSEP-HD cohort is to propose for the first time a database for the national and international community of researchers in MS, from fundamental studies of biomarkers to projects in public health. In parallel with these objectives, relevant methodological challenges must be addressed to improve the quality of results.

## Cohort description

### Study design

#### The OFSEP-HD cohort

The OFSEP-HD cohort is nested in the OFSEP cohort. Patient enrolment started on 10 July 2018 and ended on 11 September 2020 in 25 French MS centres. Individuals were eligible if they had (1) a diagnosis of MS according to the most recent criteria at entry into the HD cohort,^24^ (2) were ≥15 years old at inclusion, (3) had an MS diagnosis after the study start or, if MS onset occurred before the study start, had at least one visit every 2 years after follow-up in an MS centre with prospective OFSEP data collection; (4) had an irreversible Expanded Disability Status Scale (EDSS) score ≤7.0 (permanent use of a wheelchair) at inclusion in the study and (5) signed a written consent form. The criterion 3 for MS onset date allowed for mixing incident and prevalent cases, accelerating recruitment while benefiting from quality data collected during the OFSEP cohort follow-up, extending the possibility to fund the follow-up of included patients over time and increasing the probability to observe landmarks. Non-inclusion criteria were an inability to answer questionnaires and pregnancy at the time of inclusion (figure 1).

**Figure 1 F1:**
[figure not shown]
OFSEP-HD cohort recruitment flow diagram. HD, high definition; MS, multiple sclerosis; OFSEP, Observatoire Français de la Sclérose en Plaques.

With a sample size of 2842 patients, a factor with a HR of 1.2 could be detected if the event rate was 30%, and one with a HR of 1.6 could be detected if the event rate was 5% (power=0.8; α risk=0.05; SD=0.5).^25^ We acknowledge that our power calculation does not account for multiple testing, as do other cohorts with many exploratory objectives.

This protocol is registered at ClinicalTrials.gov: NCT03603457.

#### The OFSEP cohort

The French OFSEP cohort is a nationwide systematic longitudinal study of individuals with MS followed in MS centres with more than 70 000 patient records collected in June 2018. The first objective was to provide a unique source of information on MS epidemiology, with a particular focus on pharmacoepidemiology of recently introduced DMTs. Since 2011, the centres have collected data with a standardised form as well as a minimal set of mandatory clinical data.^23^ They collect, organise and maintain the clinical database by using the MS-specific EDMUS software.^26^ In 2015, the OFSEP MRI working group published recommendations on the sequences to be used for regular brain and spinal cord MRI acquisitions of patients with MS,^27 28^ and standardised acquisition protocols have been disseminated. Pseudonymised MRI data are transferred to a centralised imaging resource centre, the Shanoir platform (http://shanoir.org). Moreover, biological samples are collected for a subsample of OFSEP patients and stored in a biobank.^29^

#### Multisource data collection

During the inclusion visit in OFSEP-HD, historical clinical data were collected from medical records if they were incomplete from the OFSEP database, including oligoclonal bands and IgG index from cerebrospinal fluid at diagnosis. The OFSEP-HD follow-up visits are annual, with a time window of ±2 months around the anniversary inclusion date. In case of detection of recent disease activity (see landmarks paragraph below), a new baseline assessment at this key step of the disease (rebaseline) will be done, which will lead to restarting the annual follow-up (figure 2). The rebaseline process is allowed only once for a patient.

**Figure 2 F2:**
[figure not shown]
Design of the OFSEP-HD cohort. CSCT, Computerised Speed Cognitive Test; HD, high definition; 9HPT, 9-Hole Peg Test; OFSEP, Observatoire Français de la Sclérose en Plaques; T25FW, Time 25-Foot Walk.

Four main landmarks are considered, corresponding to four strategic times in the MS evolution: (1) the first visit when the diagnosis of MS is set; (2) the first visit when the diagnosis of progression (primary or secondary) is set; (3) any visit with recent disease activity, defined by the occurrence of a relapse and/or MRI activity detected with gadolinium enhancement in the past 3 months (or gadolinium-enhanced lesion in the 3 months after an annual visit) and (4) any visit with absence of disease activity in the past 5 years.

At the inclusion and annual OFSEP-HD follow-up visits, the following multisource data are collected. First, the investigators oversee the collection of sociodemographic data, geographic residence, geographic area of origin, neurological episodes, EDSS, DMTs (date of onset and stopping, reasons for stopping), serious adverse events (OFSEP minimal report form), standardised brain and whenever possible spinal cord MRI results following OFSEP recommendations for MRI acquisitions,^27 28^ and additional clinical evaluation with Time 25-Foot Walk, 9-Hole Peg Test^30^ and Computerised Speed Cognitive Test.^31^ They also collect brain MRI results obtained in one of the labelled centres using the OFSEP acquisition protocols in a 3-month period before or after the inclusion visit and in a 2-month period before or after the follow-up visit. This time window is necessary to not undermine the routine follow-up of the patient, but special attention will be paid to organise the MRI examinations as close as possible to the visits. Biological samples (blood, serum) were collected at inclusion for constitution of a biobank^29^ and to dose (1) biomarkers (neurofilament light chain (NFL), Tau, Glial fibrillar acidic protein (GFAP), ubiquitin C terminal hydrolase L1) with Simoa Human Neurology 4-Plex assay and every 2 years with 2-Plex (NFL, GFAP) of Quanterix, which detects subpicogram levels of biomarkers, a very sensitive (limit of 0.32 pg/mL) and reproducible (coefficient of variation in the 10% range) method, (2) vitamin D with mass spectrometry, which is very sensitive and reproducible and (3) genetic ancestry. When necessary, we will use a part of the historical OFSEP biological collection. Establishing such a biological collection will allow to assess other markers (eg, EBV status) and help validate new serum biomarkers of MS in the future (eg, other neuronal or glial markers, cholesterol, oxidative stress, cytokine profile, auto-antibodies) as well as persistent organic pollutants possibly involved in the progression of MS.

Second, patient self-reporting questionnaires will be used to assess PROs (see below).

Third, the OFSEP-HD cohort will be linked to the French Système national des données de santé (SNDS) claims database registering all data for reimbursed health prescriptions and hospital stays covered by the national health insurance system.^2 32^ Sick leave and disability status/pension will be obtained from the SNDS as will use of healthcare (specific to and apart from MS), and geographic location with related socioeconomic variables and access to care.

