#### Statistical analysis strategy

Several prognostic models will be developed and validated. The model development will be based on a training cohort consisting of a random selection of two-thirds of the centres. The above list of prognostic factors (ie, first, sociodemographic, clinical, imaging, biological variables and comorbidities and second, treatments and the four landmarks) will be considered as three blocks. The prognostic factors will be considered to achieve dynamic predictions^50^ of the following times to events: reaching irreversible EDSS scores of 4, 6 and 7; first relapse; disease progression; MRI outcomes; PROs (QoL), social consequences and combined outcomes of clinical and MRI data reflecting activity and disease progression.

To consider the longitudinal predictors up to the landmark time, we will adapt the methodology proposed by Devaux *et al*.^51^

According to data from the remaining one-third of centres in the external validation cohort, we will use several metrics to appraise the predictive capacities of the models. We will randomise centres and not individuals for learning and validation, because the latter strategy would have been considered as internal validation, questioning the generalisation of the results.^52^

In a stratified medicine perspective, we aim to develop stratified algorithms for medical decision-making for maximising the number of years without disease progression and with the best QoL, this last dimension depending on both the disease activity and the treatment adverse events. The knowledge gained will allow for a clear picture of the history of MS in the 2010–2020s and the various determinants of outcomes. This landmark approach will identify some prognostic factors that play a permanent role and others to be considered at some stages of the disease course for more appropriate decision-making for care, regardless of treatment. We will study the potential of the new classification of disease activity and progression to modify the prognostic classification of cases initially developed using the classical progressive relapse secondary progressive classification.

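### Landmark 3 lets an enhancing lesion found after an annual visit give that visit its landmark status, so activity outcomes can be predicted from their own future unless time zero is moved to the scan or rebaseline

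*Protocol article*

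**What the plan says.** All references are to the protocol article.

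- **Landmark definition** (Multisource data collection, text after the Figure 2 caption). The four landmarks are introduced as strategic times, and each is described as a visit. The third is "any visit with recent disease activity, defined by the occurrence of a relapse and/or MRI activity detected with gadolinium enhancement in the past 3 months", followed by the extension "or gadolinium-enhanced lesion in the 3 months after an annual visit".
- **Rebaseline** (same section). When recent activity is detected, "a new baseline assessment at this key step of the disease (rebaseline) will be done, which will lead to restarting the annual follow-up". A limit follows: "The rebaseline process is allowed only once for a patient".
- **MRI collection** (same section). Brain MRI is collected "in a 3-month period before or after the inclusion visit and in a 2-month period before or after the follow-up visit". The stated reason is to fit routine care, and "special attention will be paid to organise the MRI examinations as close as possible to the visits".
- **Models** (Statistical analysis strategy). The landmarks are listed among the blocks of prognostic factors. The predicted times to event include irreversible EDSS 4, 6 and 7, and also "first relapse; disease progression; MRI outcomes; PROs (QoL), social consequences and combined outcomes of clinical and MRI data reflecting activity". On predictor timing, the section begins its sentence on method with "To consider the longitudinal predictors up to the landmark time".
- **Frequency at inclusion** (Findings to date). Relapse or MRI activity in the past 3 months was documented in 25.5%, with 369 values missing.

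**The concern.** A landmark prediction is valid when everything that decides who is in the landmark group is known at the landmark time. The first part of the definition looks back and meets this condition. The parenthesis looks forward up to 3 months and does not, if the visit is the time origin.

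Two things are then at stake. First, early activity risk in the landmark-3 group is inflated, because patients admitted by the later lesion may have an event soon after time zero by virtue of how they were admitted. Landmark status would look more prognostic for activity than it is. Second, the model would not match its intended use. The Introduction wants prognosis at the moment the neurologist decides on management, and at that visit the qualifying scan does not yet exist.

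The planned validation in the remaining third of centres would not expose this, because those centres apply the same definition.

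**Working it through.** No figure in the article carries this point, so there is none to reproduce. The check is one of time order, followed by two illustrations of size.

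**Time order for a patient whose enhancing lesion is found after an annual visit**

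1. Annual visit at month 0, with no relapse or enhancing lesion in the preceding 3 months. The backward-looking part of landmark 3 is not met.
2. A scan at some month between 0 and 3 shows an enhancing lesion. By the parenthesis, landmark 3 is now met.
3. Which date is the landmark time? The definition names a visit. Nothing in the article names the scan date or the rebaseline visit as the landmark time.
4. If it is month 0, the lesion of step 2 lies in the outcome period. It can count towards MRI activity or a NEDA-type composite.
5. If it is the scan date or later, the lesion is history and there is no look-ahead.

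The forward window in the landmark definition (3 months) is also longer than the follow-up MRI collection window (2 months), so the two rules do not coincide.

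**Illustration A: absolute risk.** Let f be the fraction of landmark-3 entries made only by the post-visit route, and r the true one-year activity risk. Both are assumptions: f = 10% to 30%, r = 30%. If every post-visit entry counts as an event, the estimated risk is f + (1 − f) × r.

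- f = 0.10: 0.10 + 0.90 × 0.30 = 0.37
- f = 0.20: 0.20 + 0.80 × 0.30 = 0.44
- f = 0.30: 0.30 + 0.70 × 0.30 = 0.51

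The excess over r is f × (1 − r), that is 7, 14 and 21 percentage points.

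**Illustration B: spurious prognostic value.** Assume a constant activity rate, the same for everyone, so that landmark status truly predicts nothing. Let p be the probability of activity in any 3 months (assumed). A visit is flagged if activity occurs in the 3 months before or after it, and the clock starts at the visit.

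- Flagged: F = 1 − (1 − p)²
- Flagged only by later activity: p(1 − p)/F
- 12-month risk if unflagged: U = 1 − (1 − p)³, since the first 3 months are event-free by definition
- 12-month risk if flagged: p/F + (1 − p/F) × U

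At p = 0.10: F = 0.19, U = 0.271, flagged risk = 0.526 + 0.474 × 0.271 = 0.655, ratio = 2.4.

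| p (assumed) | Flagged only by later activity | Risk, flagged | Risk, unflagged | Ratio |
|---|---|---|---|---|
| 2% | 0.495 | 0.534 | 0.059 | 9.1 |
| 5% | 0.487 | 0.582 | 0.143 | 4.1 |
| 10% | 0.474 | 0.655 | 0.271 | 2.4 |
| 15% | 0.459 | 0.718 | 0.386 | 1.9 |
| 25% | 0.429 | 0.819 | 0.578 | 1.4 |

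With a flag that looks back only, the ratio is 1.00 by construction. It is also 1.00 if the clock starts at or after the qualifying scan. Illustration B is a strong case: it treats all activity as detectable on both sides of the visit, whereas the article's post-visit route admits only enhancing lesions.

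**The case against.** The strongest reply is that the article never states that the clock starts at the annual visit for this route. Detected recent activity triggers a new baseline and restarts annual follow-up, so the parenthesis may exist to capture such patients for rebaseline, with the clock starting after the lesion. The models also restrict longitudinal predictors to the period up to the landmark. The design figure is not shown, and a condensed article may leave exact date variables to a fuller document.

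This stands in part. Look-ahead is conditional on the time origin, and rebaseline can remove it for a first episode. It does not settle the matter, for three reasons. Rebaseline happens once per patient, while landmark 3 applies to any qualifying visit. The rebaseline visit is not said to be the landmark time. And a limit on predictor histories does not govern how landmark membership is decided. The point rests on a definition the article states, and does not depend on a detail it omits.

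Three stronger readings are tempting and are not supported:

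- **That post-visit scans enter the models as predictors known at the visit.** The MRI windows are rules for collecting data. No text makes them a modelling rule.
- **That all outcomes are contaminated by construction.** An enhancing lesion is not a relapse as defined under Clinical outcomes, and it does not by itself meet an irreversible EDSS, quality-of-life or social outcome. Even the MRI outcomes section does not list enhancement among its examples, though that list is not exhaustive. If the post-visit scan serves as the reference scan, the lesion need not be counted as new.
- **That the 25.5% at inclusion shows how many patients are affected.** It is reported for the past 3 months only, whereas the post-visit route is worded for annual visits.

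**Conclusion.** The concern holds in conditional form. As written, later information can decide landmark-3 membership. If the visit is time zero, which is the natural reading of a landmark defined as a visit, the same lesion can count as an early event in MRI-activity or NEDA-type outcomes. The effect on relapse, irreversible EDSS and patient-reported outcomes is indirect.

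The size cannot be found from the documents. The 37% to 51% and the ratios of 1.4 to 9.1 rest wholly on assumed f, r and p, on the clock starting at the visit, and on the qualifying lesion being counted as an outcome. They show that the artefact could be material. They do not show that it will occur. A reader might infer that leakage is an established fact of the plan, but the article does not fix the time origin in a way that proves it.

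**What to change.** State in the analysis definitions:

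1. For landmark 3 reached by a post-visit lesion, time zero is the date of the qualifying scan or the rebaseline visit that it triggers. Choose one and apply it throughout. Say what applies to later episodes, when rebaseline has already been used.
2. Only outcomes occurring after time zero count. The qualifying lesion is history.
3. An MRI is used as a predictor only if dated on or before time zero.

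The change is the redefinition of one date variable from MRI dates, and it can be made before the models are fitted, since follow-up runs to December 2026. The cost with the scan date is up to 3 months of follow-up for the affected patients, whose clinical and questionnaire data from the annual visit would be up to 3 months old at time zero. If the rebaseline visit is chosen, the interval from scan to that visit is added; the article does not give its length. Reporting how many landmark-3 entries come only by the post-visit route would replace the assumed f with an observed value.
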